### Sample size

A power calculation was carried out to estimate sample size according to the following equation:
$$ \mathrm{N}=\frac{2F{\sigma}^2}{d^2}. $$

where N = sample size, *σ* = standard deviation, *d* = difference, and *F* = constant related to statistical power and confidence interval.

A previous similar study was able to detect significant and clinically important differences in weight Z-score (*σ* = 0.8, d = 0.63) and stress score (*σ* = 4.4, d = 3.51) in response to the same relaxation intervention (meditation audio) but in mothers of healthy term infants. Our sample of breastfeeding mothers of LPI might be more stressed and thus may respond less to the relaxation intervention. Therefore, a sample of 68 mothers (34 randomised to each group) is adequate to detect a three-point difference in stress score and a 0.55 weight Z-score difference significant at 5% with a power of 80%. This may be a challenging population and mothers may not complete the study measurements; therefore, accounting for that and drop-outs, we aim to recruit a sample of 80 mother–infant pairs.

### Research procedures

#### Recruitment (0–2 weeks post-delivery)

Participants will be identified mainly from the Royal Free Hospital, Barnet Hospital, and University College London Hospital. The study flyer will also be advertised on social media. The main researcher will provide interested mothers with participant information sheets and confirm their eligibility. Informed consent will be obtained at the first home visit.

#### Follow-up screening by telephone (1–2 days prior to first home visit due date)

Mothers will be contacted a few days before the first home visit to determine if they are still eligible to participate. They will be asked whether they are still breastfeeding and intending to continue breastfeeding for at least 6 weeks. If still eligible, the time of the first home visit will be confirmed and mothers will be reminded of the preparations required for the breast milk and saliva sample collection.

#### First home visit (HV1; 2–3 weeks post-delivery)

At the first home visit, saliva and breast milk samples will be collected using standardised methods. Anthropometric measurements including infant’s weight and length and mother’s weight will be taken. The main researcher (SD) will also conduct the Rey Auditory Verbal Learning Test (RAVLT) to assess the mother’s verbal memory. The Neonatal Questionnaire will be administered during the home visit to assess early hospital practices such as timing of breastfeeding initiation, skin-to-skin contact duration, type of delivery, and feeding practices at the hospital.

To reduce the burden of form filling on the participants, a study folder containing the following questionnaires will be left at the participant’s home to be filled at the mother’s convenience in the three subsequent days:
Perceived Stress Scale (PSS) and Edinburgh Postnatal Depression Scale (EPDS)Perception of Insufficient Milk Questionnaire (PIMQ)Maternal Attachment Inventory (MAI)Maternal Responsiveness Questionnaire (MRQ)Breastfeeding Status Questionnaire adapted from the CDC Infant Feeding Practices Study II QuestionnairesBaby Eating Behaviour Questionnaire (BEBQ)3-Day Infant Behaviour DiaryDemographic questionnaire

Finally, an infant weighing scale and log will be given to the participants to complete 48 h of test-weighing to assess average milk consumption.

#### Randomisation and blinding

After the first home visit, each mother will be randomly allocated to either the intervention group (relaxation therapy) or control group. Randomisation assignments will be prepared by a member of the research team, who will have no contact with the mothers, using a computer-generated list stratified for gestational age and parity. Assignments will be stored in sealed opaque envelopes. The assignment will be revealed 3 days after the first home visit when the researcher will retrieve the infant weighing scale from the participant and provide mothers in the intervention group with the meditation tape and meditation use log. To avoid contamination between the intervention and control group, mothers will not be informed about this process until the end of the study, when they will all be offered the meditation.

#### Second home visit (6–8 weeks post-delivery)

The same research procedures will be carried out at the second home visit and the mothers will be asked to complete the same questionnaires, except for the neonatal and demographic questionnaires.

Participants will be reimbursed (£30 voucher) for their time at the second home visit, which might encourage them to complete the follow-up.

#### Telephone/online follow-up (3 and 6 months post-delivery)

Breastfeeding success and intensity will be assessed using the Breastfeeding Status Questionnaire. Information about solid food introduction will also be collected.

### Intervention

Mothers in the intervention group will be given a breastfeeding meditation recording and instructed to listen to it during breastfeeding or pumping. The audio is based on a guided imagery meditation originally developed by Sheri Menelli in 2001 [35] and previously used in three RCTs [32–34]. The audio that will be used is 8 min in duration and has been adapted to suit the current population. Mothers will be encouraged to use it as many times as they would like, but at least once a day for the first 2 weeks starting at HV1 (2–3 weeks post-delivery). They will also be asked to keep track of the frequency and dates the meditation audio was used in the listening logs provided.

#### Pilot study

A within-subject pilot study was conducted at University College London to compare the effectiveness of five different relaxation interventions (guided-imagery meditation audio, music listening, relaxation lighting, combination of relaxation lighting and guided-imagery meditation, combination of relaxation lighting and music listening) and one control (silence/sitting) in 17 women of reproductive age. Subjective feelings of relaxation (ten-point scale), heart rate, systolic and diastolic blood pressure, and fingertip temperature were measured before and after each technique. Based on the results, meditation was selected as the most appropriate intervention for use with breastfeeding mothers of LPI.

### Control

Participants in the control group will receive no intervention and will be informed that the purpose of the study is to investigate the factors that influence breastfeeding in mothers of LPI and to study mother–infant signalling through breastfeeding. All participants will be informed of the randomisation process after completion of the trial and control mothers will be offered the intervention.

### Outcome measures

#### Primary outcome measures

##### Maternal stress

PSS will be used to assess maternal stress levels at both home visits; a ten-item scale, it is used to assess the extent to which someone’s life is seen as stressful and uncontrollable [36]. Each item is scored on a five-point scale (0–4) and thus the total could range from 0 to 40. Higher scores indicate higher stress. The PSS has been validated in English and has a Cronbach’s alpha of 0.85 [36]. It has also been widely used in studies, including three national surveys in the US [37] and a previous similar trial for breastfeeding women [34].

##### Infant weight

Weight will be measured using a digital infant weight scale (Seca, UK). Infants will be weighed naked and pre-feeding, if possible. Measurements will be taken two times, and the mean of the two values will be used to calculate weight Z-score for analysis.

#### Secondary outcomes

##### Breast milk composition

Breast milk samples will be collected for macronutrient and hormone analysis. Mothers will be asked to collect milk with the use of their electric or manual pump. If they do not own one, they will be provided with a manual pump (Philips AVENT, Philips, The Netherlands). Khan et al. showed that fat content varied significantly over a 24-h period, being highest at mid-morning, and was associated with the degree of breast fullness/emptying [38]. Therefore, participants will be asked to provide a full expression from a breast that has been emptied in the previous feeding session with at least 2-h wait. All home visits will take place in the morning and breast milk will be collected at 11:00 h ± 1.5 h. These measures will ensure that the sample provides the closest indication of nutrient per feed and reduces the between- and within-subject variability in milk composition. If possible, a volume of 15 ml will be transferred to 5 ml and 1.5 ml tubes, and the remaining milk in the collection bottle will be returned to the mother for feeding later/immediately. The samples will be transferred in a freezer bag with frozen ice packs from the participant’s home to − 80 °C storage until analysis. Macronutrients will be analysed using the MIRIS Human Milk Analyser (Miris, Sweden), while the hormones (ghrelin, leptin, adiponectin, cortisol) will be analysed using an enzyme-linked immunosorbent assay kit.

##### Breast milk supply

The volume of breast milk consumed over a period of 48 h will be determined using the test-weighing method. Mothers will be instructed to weigh their baby before and after each feeding using the electronic baby scale provided by the researcher. The participants will be asked to change the infant’s nappy before taking the first measurement. Measurements will be recorded by the mother on the test-weighing log provided, including the duration of the feed. Correction will be made for insensible water loss during the feed [39]. Several studies have shown that test-weighing before and after a feed, whether it is formula feeding or breastfeeding, is a valid method especially when using an electronic scale [40]. It was also shown to be useful in research, clinical, and home settings. A breastfeeding log will be provided, including the timings and durations of the feed, to help us estimate breast milk intake in case of missing weighings.

##### Infant length

Length and infant weight will be taken to measure infant growth. Recumbent length will be assessed using an infant length measuring mat. All infants will be placed in a supine position with their head against the headboard and the base of their feet against the vertical plate. The BMI will also be calculated (weight (kg)/length (m^2^)). Length and body mass index Z-scores will be calculated for analysis.

##### Infant behaviour

Infant eating behaviour and appetite will be assessed using the BEBQ. It is an 18-item parent-reported questionnaire that measures overall appetite and assesses four eating traits: ‘enjoyment of food’, ‘food responsiveness’, ‘slowness in eating’, and ‘satiety responsiveness’ [41]. These traits might be related to infant weight gain and might be altered with maternal psychological distress (possibly meditated through breast milk composition).

Infant crying and sleeping will be measured using a 3-day infant behaviour diary, which was previously validated against audiotapes and against actigraphy and showed good compliance [42]. The 72-h diary is divided into 15-min segments, where the mother will be asked to indicate whether the infant was crying, sleeping, feeding, being fussy, or was awake and content.

##### Mother–infant attachment

The MAI, consisting of 26 items, will be used to measure the attachment between each participant and her baby. Each statement is marked on a four-point Likert scale. The sum of the 26 questions will yield the total score, where higher scores indicate better attachment. It demonstrated a Cronbach’s alpha of 0.85 when used to measure maternal attachment with 4-week old infants [43].

##### Maternal depression

Maternal depression will be assessed using the EPDS, a ten-item self-administered scale [44]. Each item is scored on a four-point scale (0–3) with total scores ranging from 0 to 30. Higher scores indicate a higher intensity of symptoms experienced during the previous week. EPDS has been validated in English and has a Cronbach’s alpha of 0.86.

##### Cognitive function

Maternal verbal learning and memory will be evaluated using RAVLT to assess the ‘baby brain’ phenomenon. It consists of five recall trials (trials 1–5) using list A (15 noun word list) and one recall after an interference period (trial 6) using list B (another 15 noun word list). The outcomes of the test will include: immediate recall (sum of correct responses after first five trials) and verbal learning (difference in number of correct responses after trial 5 and trial 1) [45].

##### Perception of milk supply

PIMQ, a self-report, six-item scale, will assess maternal perception of insufficient milk supply [46]. The first item of the questionnaire will ask whether the participant believed she had sufficient milk to satisfy her infant (yes/no). This is followed by five questions relating to the reasons for this belief, measured on a ten-point Likert scale ranging from 0 (strongly disagree) to 10 (strongly agree). Higher scores indicate higher perception of having adequate milk. PIMQ showed good internal consistency with a Cronbach’s alpha of 0.70.

##### Maternal responsiveness

Maternal responsiveness to infant cues will be assessed using the MRQ. MRQ measures the extent to which mothers respond promptly to their infants across different situations [47].

##### Salivary hormones

Saliva samples for hormone analysis will be collected using the passive drool method where the mother will transfer 500 μl saliva into a 1.5 collection tube using a Saliva Collection Aid (Salivette, Sarstedt, Germany). Samples will be transferred in a freezer bag with frozen ice packs from the participant’s home to − 80 °C storage until analysis.

### Data management, monitoring, and dissemination

Identifiable data (hard copy) collected, including contact data, will be stored in locked filing cabinets at the Institute of Child Health separate from other study data. All data collection forms, questionnaires, and labels will include only the participant study ID number. These pseudo-anonymised forms will be stored in filling cabinets at University College London. Breast milk and saliva samples collected will be stored in a locked nutrition freezer unit. The results of the study will be published in peer-reviewed journals and will be presented at scientific conferences. No identifiable data will be published or presented to maintain the anonymity of the participants.

There are no arrangements for a formal data monitoring committee to be convened since the study is of short duration and the intervention is not considered to pose any risk.

### Statistical analysis

Data will be entered and analysed on SPSS v23.0. Kolmogorov-Smirnov test will be used and histograms and Q-Q plots will be assessed to test for normality. Results will be considered statistically significant at *p* < 0.05. The main analysis of the randomised controlled trial results will be an intention-to-treat analysis, but we will also be looking at whether there is a ‘dose–response’ effect between the use of the audio and the outcomes. For the primary outcomes, the differences in weight Z-score and PSS score between groups will be analysed using independent sample *t*-test, taking into account the baseline weight and stress scores (Supplementary Table 1). Similarly, for the secondary outcomes, differences between control and intervention in milk composition, milk supply, maternal cognitive function, maternal salivary cortisol/oxytocin, EPDS score, mother–infant attachment, and infant behaviour will be analysed using independent sample *t*-test. As a secondary analysis, the relationship between breast milk hormones and infant behaviour, growth and sex and maternal anthropometric measures will be analysed using univariate regression, while adjusting for confounding factors such as randomisation status, gestational age, and bottles of formula fed in the previous 7 days (Supplementary Table 1).

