## Methods/design

### Study design

The Mother and late Preterm Lactation Study (MAPLeS) is an RCT using a breastfeeding meditation for breastfeeding mothers of LPI. Participants will be identified from multiple hospitals with the capacity to care for LPI in London, UK. Eligible mothers will be randomly allocated to either the intervention group, where they will be asked to listen to the relaxation therapy, or to the control group where no intervention is given. The first home visit will be conducted at 2–3 weeks post-delivery, when treatment will commence. At this time point, it is likely that LPI would be discharged from the hospital and that breastfeeding would be somewhat established. One of the main aims of the study is to investigate mother–infant signalling through breastfeeding; therefore, it is important to target women who are more likely to be breastfeeding for the duration of the study. The second home visit will be at 6–8 weeks post-delivery for follow-up. At both time points, questionnaires, breast milk and saliva samples, and anthropometric measurements will be collected. We will also follow-up at 3 and 6 months post-delivery by email or phone to assess breastfeeding status. The SPIRIT figure and study design flow chart are shown in Figs.1 and 2.

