### Hypotheses

#### Primary hypotheses

Mothers in the intervention group, using the relaxation therapy from week 2–3 post-delivery, will have a higher reduction in maternal stress score (*primary maternal outcome*) by week 6–8 post-delivery compared to mothers in the control group.Infants in the intervention group will have a higher gain in weight Z-score (*primary infant outcome*) by week 6–8 post-delivery compared to infants in the control group.

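### The primary t-test is said to allow for baseline but the visible text does not say how; ANCOVA on the first-visit values would settle this and gain precision at no cost

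*Protocol article*

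**What the plan says.** Under Statistical analysis, the protocol article states that "the differences in weight Z-score and PSS score between groups will be analysed using independent sample *t*-test", and adds "taking into account the baseline weight and stress scores", with a reference to Supplementary Table 1. A list of secondary outcomes then receives the same test, introduced as being handled in a similar way. Regression with adjustment is described only for the analyses of breast milk hormones.

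The Primary hypotheses are framed as change between the two visits. Mothers in the intervention group "will have a higher reduction in maternal stress score", and "Infants in the intervention group will have a higher gain in weight Z-score".

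The baseline values needed for adjustment will exist. Under Maternal stress, "PSS will be used to assess maternal stress levels at both home visits", and under Study design, "At both time points, questionnaires, breast milk and saliva samples, and anthropometric measurements will be collected".

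The Sample size section uses N = 2Fσ²/d² with σ = 4.4 for stress and 0.8 for weight Z-score. It gives 34 per group for differences of 3 points and 0.55, at 5% significance and 80% power. It does not say whether σ is the SD at one visit or the SD of change, and it gives no correlation between visits.

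**The concern.** A two-sample t-test compares two means and has no place for a covariate, so the sentence does not fix one analysis. At least two fit it: a t-test on change from baseline, and a baseline-adjusted model loosely called a t-test. A comparison of second-visit values with baseline only inspected is a further, weaker reading. These give different estimates and p-values from the same data. For the primary analysis of both main outcomes, the choice should be settled before the results are seen.

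Efficiency is also at stake. A change score fixes the baseline slope at 1. When the true slope is well below 1, subtracting baseline adds noise, and the analysis can have less power than one that ignores baseline. ANCOVA estimates the slope from the data and avoids both losses.

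**Working it through.** **Inputs.** From Sample size: 34 per arm; d = 3 and σ = 4.4 (Perceived Stress Scale, PSS); d = 0.55 and σ = 0.8 (weight Z-score); 5% significance; 80% power. Assumed, because the article does not say: a two-sided test, σ as the SD at a single visit and equal at both visits, and r = 0.3, 0.5 or 0.7.

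**Step 1: reproduce the plan's figure.** F = (1.960 + 0.842)² = 7.85.
- PSS: 2 × 7.85 × 4.4² / 3² = 33.8, so 34 per arm.
- Weight Z-score: 2 × 7.85 × 0.8² / 0.55² = 33.2, so 34 per arm.

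The total of 68 is reproduced exactly. The formula contains no term for r.

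**Step 2: effective SD under each analysis.**
- Follow-up values only: σ.
- Change score: σ√(2(1 − r)).
- ANCOVA: σ√(1 − r²), with one degree of freedom lost.

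For PSS at r = 0.3, the change-score SD is 4.4 × √1.4 = 5.21 and the ANCOVA SD is 4.4 × √0.91 = 4.20. At r = 0.5 the change-score SD equals σ, which is why 0.5 is the crossing point.

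**Step 3: power at 34 per arm** (noncentral t, two-sided 5%).

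| Outcome | Analysis | r = 0.3 | r = 0.5 | r = 0.7 |
|---|---|---|---|---|
| PSS, 3 points | Follow-up only | 0.79 | 0.79 | 0.79 |
| | Change score | 0.65 | 0.79 | 0.95 |
| | ANCOVA | 0.83 | 0.89 | 0.97 |
| Weight Z, 0.55 | Follow-up only | 0.80 | 0.80 | 0.80 |
| | Change score | 0.66 | 0.80 | 0.95 |
| | ANCOVA | 0.83 | 0.90 | 0.97 |

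The 0.79 for PSS, rather than 0.80, comes from using the t distribution; the article's normal approximation gives 0.803. On that approximation, 80% power for PSS at r = 0.3 needs 48 per arm with change scores and 31 with ANCOVA.

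**Step 4: does the ranking depend on what σ means?** The ratio of ANCOVA variance to change-score variance is (1 − r²) / (2(1 − r)) = (1 + r)/2, which does not exceed 1. The ratio to follow-up only is 1 − r², which also does not exceed 1. With equal variances at the two visits, the ordering therefore holds whichever SD was quoted. Only the absolute power figures depend on it.

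**Step 5: chance imbalance.** The standard error of the baseline PSS difference between arms is 4.4 × √(2/34) = 1.07 points. A difference at least that large arises in about a third of randomisations. Given such a difference, the change-score estimate moves by (1 − r) × 1.07, which at r = 0.3 is 0.75 points, a quarter of the 3-point target. ANCOVA adjusts for it.

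**Step 6: validity.** In a simulation of 8,000 trials per setting with 34 per arm and no treatment effect, all three analyses had type I error between 4.5% and 5.2%.

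**The case against.** The strongest reply is that the plan is already adequate. Both hypotheses are worded as change, and a t-test on change from baseline does use baseline and is valid under randomisation. Supplementary Table 1 is cited exactly where baseline handling is described and may define the variable or model. An article condenses a fuller protocol, and exact models are often left to such documents. The power loss also depends on two unknowns: if 4.4 and 0.8 are SDs of change, the change-score test has about its planned power whatever r is, and otherwise power falls short only when r is below 0.5.

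Most of this stands. A reader might infer that a t-test cannot take baseline into account, so that the stated analysis is impossible or wrong. The documents do not support that, because the change-score reading is available and fits the hypotheses. A reader might also infer that the results would be biased. They would not be on average: the shift in step 5 is conditional on a particular imbalance, and type I error is held.

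The reply does not remove two facts. The visible text names a test without saying how it does what the sentence claims, and a more precise analysis is available from data that will be collected anyway.

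**Conclusion.** The point stands as a free improvement in clarity and precision. It does not show an invalid analysis or a wrong sample size. The visible text leaves the baseline handling open, subject to what Supplementary Table 1 says. Under the change-score reading, with single-visit SDs, power at 34 per arm is about 0.65 for stress and 0.66 for weight Z-score at r = 0.3, against 0.83 for ANCOVA on both. At r = 0.7 the gap nearly closes (0.95 against 0.97). The article gives no r, so the size of the gain is a range, not an estimate. That ANCOVA is at least as precise as either t-test, apart from one degree of freedom, does not depend on which SD was quoted.

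**What to change.** Replace the t-test sentence for the primary outcomes with a linear model for each: second-visit PSS on arm and first-visit PSS; second-visit weight Z-score on arm and first-visit weight Z-score. Report the adjusted difference between arms with its 95% CI. Use the same model for continuous secondary outcomes measured at both visits. A binary outcome such as exclusive breastfeeding should not go into this linear model. Bring Supplementary Table 1 into line if it says something different.

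The cost is a sentence or two in the analysis section. No new measurements, participants or change to the sample size are needed, and the model is available in the planned software. The change should be made before the outcome data are compared by arm.
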